#### Statistical analysis plan

Data will be collated, cleaned and validated, using programmed edit checks, in a database that will be locked prior to the unblinding of the study statistician. The primary analysis will take place after all subjects, not known to have withdrawn or not deemed lost to follow-up, have had their 12 months assessments, based on the intention-to-treat principle (i.e. subjects’ data are analysed as randomised and as stratified). A “per-protocol” sensitivity analysis will be restricted to those subjects with at least one post-baseline assessment and, for subjects randomised to the R2C arm, participation in at least one structured telephone counselling session.

The repeated measurements of the outcome variables will be analysed by fitting linear mixed models, with fixed effects for treatment and time, and their interaction, and random effects for subjects and assessments within subjects, using restricted maximum likelihood (REML). As well as accommodating missing values under the missing at random assumption, this method will allow the most suitable variance-covariance model for the repeated measures to be selected, using Akaike’s information criterion [63], and commonality of nonlinear trends over time to be explored via splines. The *F* test will be used to test for an overall group-by-time interaction, and the primary comparison, between groups, of their changes from baseline to 3 months follow-up will be based on a *t* test of the corresponding interaction contrast — this *t* test will utilise the predicted means and their variance-covariance matrix that are recovered from the fitted mixed model. Diagnostic plots of residuals will be assessed and, if deemed necessary, variance-stabilising transformations, such as the empirical logistic transformation, will be applied to the outcome variables and inferences will be based on the analyses conducted on the transformed scale. In a series of exploratory analyses, mixed models with covariates for gender, illicit drug use, extent of exposure to the intervention, exposure to other treatments or programs, level of psychological distress and, as appropriate, level of alcohol use at baseline will be fitted, including their interactions with treatment group, in order to identify moderating factors. A sensitivity analysis, to assess the impact of missing 3-month data on the primary outcome, will use a “tipping point” approach [63]. Categorical, ordinal and binary outcomes will be analysed in a similar way using generalised linear mixed models (GLMMs). The complete list of candidate covariates and details of the analyses will be specified in a statistical analysis plan that will be reviewed and approved by the Principal Investigator prior to database lock. Analyses will be conducted using the most appropriate procedures in GenStat, R and STATA.

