**Methods/design:**

This is a single site, parallel group, two-arm superiority RCT. We will recruit 344 participants from across Australia with problem alcohol use. After completing a baseline assessment, participants will be randomly allocated to receive either the Ready2Change (R2C) intervention (*n* = 172, four to six sessions of structured telephone-delivered intervention, R2C self-help resource, guidelines for alcohol consumption and stress management pamphlets) or the control condition (*n* = 172, four phone check-ins < 5 min, guidelines for alcohol consumption and stress management pamphlets). Telephone follow-up assessments will occur at 4–6 weeks, 3 months, 6 months and 12 months post-baseline. The primary outcome is the Alcohol Use Disorders Identification Test (AUDIT) score administered at 3 months post-baseline. Secondary outcomes include change in AUDIT score (6 and 12 months post-baseline), change in number of past-month heavy drinking days, psychological distress, health and wellbeing, quality of life, client treatment evaluation and cost effectiveness.

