### Randomisation

Participants will be randomly assigned to the R2C group or the control group with a 1:1 allocation ratio. Randomisation will be stratified by gender and will use a standard computer-generated “permuted blocks of variable size” scheme for each stratum. Randomisation lists for each stratum will be generated at the start of the study by the study statistician and linked to a unique identification code. The statistician who prepares the lists will play no other role in the delivery of the interventions. Allocations will be concealed in individual envelopes labelled with the unique identification code and opened (in consecutive order) by the designated researcher (Researcher 1) after the baseline assessment. Envelopes were used because at the time of trial design and start-up it was not feasible to implement a centrally managed, online randomisation system. The contents of an envelope cannot be discerned without opening the envelope, and monitoring of randomisation dates and within-stratum sequence numbers is conducted to ensure randomisation errors do not occur. Randomised participants will be assigned their unique identification code, which will be in a re-identifiable format. Participants’ identifying information collected during this study will be stored separately from trial data, while the unique identifying code will be attached to both. Participant information and trial data will be stored in separate locked filing cabinets located on the study premises.

Following randomisation, participants will be contacted by Researcher 1 and provided with an overview of their assigned protocol (i.e. R2C or control). Participants will not be told any details about the other intervention. Appropriate resources will be sent to the participant (*R2C intervention*: R2C self-help booklets [44, 45] + pamphlets [34, 46]; *control*: pamphlets [34, 46]). Hard copy materials will be posted to the participant (soft copy materials will be sent via email at the participants’ preference). An outbound telephone call will be scheduled within 7 days to commence the four to six R2C sessions with the participant’s dedicated R2C Counsellor (*intervention*), or to commence the four phone check-ins with Researcher 1 (*control*). The treatment period starts within 7 days of randomisation.

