**Fig. 5 Fig5:**
[figure not shown]
Control condition

In both the treatment and control conditions, the call duration will be recorded. Short Message Service (SMS) messages will be sent to remind participants of all pre-arranged telephone sessions, and five attempts at contact within 1 week will be made per scheduled phone session. R2C intervention calls will be made from Turning Point’s telephone and online services department, which is equipped with the infrastructure needed for outbound calls and call recording.

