### Statistical methods

#### Sample size estimation

A pilot study of an earlier version of the telephone-delivered intervention examined outcomes to a 3 month follow-up [42]. Thirty-four individuals concerned about their drinking were referred to the program and completed an average of 5.5 sessions. Participation in the intervention demonstrated significant reduction in alcohol problem severity (AUDIT score) and improvement in psychological distress (Kessler Psychological Distress Scale [K10] score). Treatment satisfaction and counsellor rapport scores were comparable to those found in face-to-face treatment. Using data from the pilot work, we found that the between-subject variance component in the AUDIT score was 23.8, the within-subject variance component was 49.8 (intraclass correlation [ICC] = 0.323) and the estimated improvement (decline) in the AUDIT score was 11.2 (standard error [SE] = 1.69). The calculation of the sample size used these estimates of the variance components, from the single-arm pilot study, and was based on the power of the *F* test for the overall time by treatment arm interaction and the power of the *t* test for the interaction contrast of primary interest, namely, baseline versus 3 months by treatment arm; calculations used the “apower” procedure for the non-central *F* distribution, and the “cut” function for the non-central *t* distribution in the GenStat statistical package [59].

We estimate, conservatively, that by 3 months, there will be an improvement (reduction of at least 8 on the AUDIT score) in the R2C arm and that the control arm could exhibit a modest improvement of 4. If these improvements are sustained at 6 and 12 months, then with 120 evaluable subjects in each arm and assuming independence between subjects and equicorrelation within subjects, the *F* test, conducted at the 5% significance level, for this treatment-by-time interaction will have 90% power (and the two-sided, 5% level, *t* test for the interaction contrast at 3 months will have 85% power). If these conjectured improvements by 3 months are not durable and, for example, deteriorate by 50% at 6 months, and the scores return, on average, to their baseline levels at 12 months, then this treatment-by-time interaction scenario will be detected with 85% power, and the power of the two-sided, 5% level *t* test for the interaction contrast at 3 months (the analysis of the primary outcome) remains unchanged at 85%.

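### The per-protocol set requires engagement in the R2C arm only, which leaves that analysis open to selection bias, probably in favour of R2C

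*Protocol article*

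**What the plan says.** The primary analysis in the Protocol article (Statistical analysis plan) is "based on the intention-to-treat principle (i.e. subjects’ data are analysed as randomised and as stratified"). The same section adds a second analysis: "A “per-protocol” sensitivity analysis will be restricted to those subjects with at least one post-baseline assessment". That condition applies to both arms. The sentence then continues with a further condition: "for subjects randomised to the R2C arm, participation in at least one structured telephone counselling session". No engagement condition is set for controls.

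Controls do have scheduled contacts. The abstract (Methods/design) gives their condition as "four phone check-ins < 5 min, guidelines for alcohol consumption and stress management pamphlets", and the Randomisation section schedules a call "to commence the four phone check-ins with Researcher 1" over the same 7-day window as the first R2C session. The Intervention section handles calls alike in the two arms: text reminders before pre-arranged sessions, five contact attempts within a week for each one, and "In both the treatment and control conditions, the call duration will be recorded".

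**The concern.** A participant can miss every counselling session and still complete a follow-up. Follow-up is done by a different researcher (Follow-up section) and is paid by voucher, whereas the Reimbursement section lists no payment for sessions or check-ins. In the R2C arm such a person leaves the per-protocol set. The corresponding person in the control arm, who takes no check-in but is assessed, stays in.

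If people who do not engage would have improved less in any case, removing them from one arm raises that arm's mean improvement without any treatment effect. The rule also works against the design of the comparator: the Choice of comparator section says the check-ins are there to balance assessment and frequency of contact, yet a control who received none of them counts as treated per protocol.

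What is at stake is interpretation. Because the analysis is called a sensitivity analysis, agreement with the intention-to-treat result, or a larger effect, could be read as confirming it. In fact it concerns a different, selected population, and the rule cannot separate selection from the effect of receiving the sessions.

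**Working it through.** **Design figures used (Protocol article, Sample size estimation).** The R2C arm is expected to show a "reduction of at least 8 on the AUDIT score" and the control arm a reduction of 4, so the design difference is 8 − 4 = 4. The within-subject variance is 49.8, with 120 evaluable per arm.

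**Reproducing the plan's figure.** The plan states that "the two-sided, 5% level, *t* test for the interaction contrast at 3 months will have 85% power".
- SD of change = √(2 × 49.8) = 9.98.
- SE of the contrast = 9.98 × √(2/120) = 1.29.
- The non-central t with 238 degrees of freedom gives 87.1% power, and the normal approximation 87.4%. The stated 85% is slightly conservative.

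This point disputes no stated figure. The check only shows that these inputs are close to those the plan used.

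**Bias with no treatment effect.** Let q be the share of *assessed* R2C participants with zero sessions. Let g be how much more starters improve than non-starters for reasons unrelated to treatment. If starters improve by s on average, the whole assessed R2C arm improves by

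(1 − q)s + q(s − g) = s − qg.

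With no effect, and with assessment itself unrelated to arm, assessed controls have the same mix and also average s − qg. The per-protocol contrast is therefore s − (s − qg) = **q × g**.

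**Illustration.** The documents give neither q nor g, so the values below are assumptions. SE = 9.98 × √(1/120 + 1/(120(1 − q))), which is 1.324 for q = 10% and 1.367 for q = 20%. The last column is 1 − Φ(1.96 − qg/SE), the chance of a significant result favouring R2C when there is no effect (nominal 2.5%).

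| q | g (AUDIT points) | Bias q × g | Share of design difference of 4 | False result favouring R2C |
|---|---|---|---|---|
| 10% | 0 | 0 | 0% | 2.5% |
| 10% | 2 | 0.2 | 5% | 3.5% |
| 20% | 2 | 0.4 | 10% | 4.8% |
| 20% | 4 | 0.8 | 20% | 8.5% |
| 10% | −2 | −0.2 | −5% | 1.7% |
| 20% | −2 | −0.4 | −10% | 1.2% |

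The last two rows show the reversal: if non-starters do better, for example because they have already cut down and decline counselling, the rule works against R2C.

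**The case against.** The shared assessment condition takes out much of the worry. Follow-ups are themselves telephone calls with five attempts, so controls who never answer the telephone also leave the set. This stands in part. A reader might infer that engaged R2C participants are compared with all controls. The document does not support that: the comparison is with assessed controls, whatever their engagement. The share that matters is therefore assessed zero-session participants, not everyone who never starts. The shared condition narrows the problem but does not remove it, because sessions and assessments are separate contacts.

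Direction and size are not shown by the documents. This stands. A reader might infer that the set is certainly biased towards R2C, or by a large amount, but there are no data on non-starters or their prognosis. The pilot even hints at a low q: its 34 participants averaged 5.5 sessions, and if six was the maximum (an assumption, since the pilot used an earlier version), at most (6 − 5.5)/6 = 8.3% had none. With that share, gaps of 2 and 4 points give 0.17 and 0.33 points of bias.

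Part of any rise in the estimate would come from removing untreated participants, which is what a per-protocol analysis is for. That is true, but the rule offers no way to tell this part from selection.

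No decision rests on this analysis, and details are left to a separate statistical analysis plan. Both are fair, and they limit the weight of the point. The inclusion rule itself, however, is stated in the article and is not among the items deferred.

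A symmetric rule is not a full cure, because taking a scripted call of under five minutes and attending counselling are different behaviours. This also stands, and it qualifies the remedy.

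**Conclusion.** The concern holds in a limited form. The per-protocol rule sets an engagement condition in one arm only, although a matching condition was available from calls that are scheduled, attempted and timed in both arms. The analysis is therefore open to selection bias, probably favouring R2C if non-starters have the poorer prognosis.

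The formula q × g assumes no treatment effect and no difference between arms in who is assessed. Its inputs are not in the documents, so 0.2 to 0.8 AUDIT points (q = 10%, g = 2 to q = 20%, g = 4) is illustrative and not an estimate. The bias is zero if g is zero and changes sign if g is negative.

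A reader might infer that the trial's main conclusion is at risk. It is not: the primary comparison is by intention to treat and does not use this rule. The point is still worth correcting, because the analysis is presented as a check on the primary result and cannot serve as one.

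**What to change.** Define the per-protocol set by the same kind of rule in both arms: at least one post-baseline assessment, and at least one completed counselling session (R2C) or at least one completed check-in call (control). Call the analysis supplementary, and state that it does not test the robustness of the intention-to-treat result.

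If the effect among those who start R2C is of interest, preferably add a complier-average causal effect with randomisation as the instrument. State its assumption openly: being assigned to R2C has no effect in those with zero sessions. The self-help booklets sent to the whole R2C arm (Randomisation section) may strain that assumption.

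The cost is one sentence, plus the extra model if it is adopted. No new data are needed, because call duration is already recorded in both arms. Slightly fewer controls enter this one analysis, and some selection remains because the two engagement behaviours differ.

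### Gender is the randomisation stratum and the analysis is promised by stratum, yet the stated efficacy model has no gender term; the effect on the primary test is small and conservative

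*Protocol article*

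**What the plan says.** The Randomisation section of the protocol article states: "Randomisation will be stratified by gender". Gender is the only stratification factor; allocation is 1:1 in permuted blocks of variable size within each stratum.

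The first paragraph of the Statistical analysis plan section sets out the intention-to-treat principle by saying that subjects' "data are analysed as randomised and as stratified".

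The next paragraph of that section gives the model for the repeated outcomes: linear mixed models "with fixed effects for treatment and time, and their interaction, and random effects for subjects and assessments within subjects". The primary comparison is a *t* test of the treatment-by-time contrast for baseline versus 3 months, computed from the predicted means of that fitted model.

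Gender comes in later in the same paragraph: "In a series of exploratory analyses, mixed models with covariates for gender" and several other variables are to be fitted, with treatment interactions, to look for moderators. The full list of candidate covariates and the analysis details are left to a separate statistical analysis plan.

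The Cost effectiveness section does adjust its regression for gender, along with the baseline value of the outcome.

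**The concern.** A model without a stratum term does not, on its face, analyse the data by stratum. A statistical analysis plan that follows the model paragraph departs from the intention-to-treat paragraph, and one that follows the intention-to-treat paragraph departs from the published model. Unless this is settled before the statistician is unblinded, both an adjusted and an unadjusted primary result can be defended from the same article.

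There is also a statistical reason to carry the stratum into the model. Stratified allocation balances gender across the arms, so the true sampling variance of the treatment contrast contains no contribution from gender. If gender predicts the quantity being compared and is left out, its contribution stays in the estimated error variance. The reported standard error is then slightly too large, and the precision that stratification was meant to buy is not used.

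**Working it through.** **Inputs from the article (Sample size estimation):** within-subject variance 49.8; between-subject variance 23.8; improvements of 8 (R2C) and 4 (control), so a difference in change of 4; 120 evaluable per arm; two-sided 5% level.

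**Assumptions, because the article gives no figure:** a 50:50 gender split, gender perfectly balanced between arms, and a difference *g* between men and women in mean 3-month AUDIT change.

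**Step 1. Reproduce the plan's own power.** For the treatment-by-time *F* test with a sustained effect, the arm differences over the four AUDIT time points are 0, 4, 4, 4. Their mean is 3 and the sum of squared deviations is 9 + 1 + 1 + 1 = 12. The non-centrality is (120/2) × 12 / 49.8 = 14.46 on 3 and 714 degrees of freedom, giving 90.5% power against 90% stated. For the 3-month contrast, the change variance is 2 × 49.8 = 99.6 and the standard error is √(2 × 99.6/120) = 1.288. The ratio 4/1.288 = 3.10 gives 87.1% to 87.4% power, depending on the degrees of freedom, against 85% stated. The stated figure is a little conservative, and this does not bear on the gender point.

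**Step 2. What a gender main effect does.** A shift by gender that is constant over visits appears in both the baseline and the 3-month score. With complete data it drops out of the change. Only a gender-by-time difference, or drop-out related to gender, is left to affect the primary test.

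**Step 3. What a gender difference in change does.** With a 50:50 split, omitting gender adds *g*²/4 to the estimated change variance, while the true variance of the contrast stays at 99.6. The reported standard error is therefore too large by the factor √[(99.6 + *g*²/4)/99.6]. Large-sample type I error is 2 × [1 − Φ(1.96 × factor)] and power is Φ(3.10 − 1.96 × factor). Beside this stand simulated change-score analyses, 20,000 trials per setting, with and without gender.

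| *g* (AUDIT points) | SE factor | Type I error, formula | Type I error, simulated | Power, formula | Power, simulated | Power with gender, simulated |
|---|---|---|---|---|---|---|
| 0 | 1.000 | 5.0% | 4.9% | 87.4% | 87.1% | 87.0% |
| 2 | 1.005 | 4.9% | 4.7% | 87.2% | 86.6% | 86.9% |
| 4 | 1.020 | 4.6% | 4.3% | 86.6% | 86.4% | 87.1% |
| 6 | 1.044 | 4.1% | 4.1% | 85.5% | 85.0% | 87.1% |

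The simulation error is about √(0.05 × 0.95/20,000) = 0.15 percentage points for type I error and √(0.87 × 0.13/20,000) = 0.24 for power. With gender included, simulated type I error was 4.7% to 5.1% over these settings.

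**Step 4. How large a gender effect would have to be.** For gender to explain a share *R*² of the change variance, *g* = 2√[99.6 × *R*²/(1 − *R*²)]. Shares of 2%, 5% and 10% need *g* of about 2.9, 4.6 and 6.7 AUDIT points. The last two exceed the whole planned treatment effect of 4.

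**The case against.** The strongest reply is that the article does not exclude gender from the primary model. The intention-to-treat wording could mean only that each subject is kept in the arm and stratum assigned, exploring gender as a moderator does not rule it out as an adjustment term, and details are deferred to the statistical analysis plan. Part of this stands: the plan could still resolve the matter. But the deferral concerns candidate covariates and details, whereas the article itself lists the fixed effects and puts gender in the exploratory work. The point is a mismatch between two published statements, and does not rest on missing detail.

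The second reply, that the statistical effect is minor, stands in full. The article gives no evidence that men and women change differently or drop out differently.

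Three stronger readings are tempting and not supported:

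- A reader might infer that the primary test is materially distorted because gender differences in drinking level stay in the residual. Those differences largely cancel from the change contrast.
- A reader might infer that heavy drinking days suffer most, because Table 2 defines them by 40/60 g. The table does not say that the two values are by gender, and even if they are, a gender-specific threshold could narrow the gender difference in the count. The gender-specific AUDIT entry cut-offs are an eligibility rule and do not alter how the outcome is scored.
- A reader might say that gender is adjusted for nowhere outside exploratory work. That holds for efficacy only, since the economic regression includes it.

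**Conclusion.** The inconsistency is plain in the text: the analysis is promised by stratum, the stated efficacy model omits the stratum, and the economic model includes it. Its numerical effect is small and on the safe side. For gender differences in change of up to 6 AUDIT points, type I error falls to no less than about 4.1% and power loses at most about 2 percentage points. Even at 6 points the simulated power of 85.0% equals the 85% that the article claims for this contrast. The result cannot be made falsely positive by this route.

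These figures rest on an assumed 50:50 split, exact gender balance between arms, complete data at 120 per arm, the pilot variance, and a change-score analysis standing in for the mixed-model contrast. The exact effect in the fitted model will depend on the covariance structure selected. Drop-out related to gender was not quantified.

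**What to change.** Before database lock and unblinding, state in the statistical analysis plan that the primary mixed model includes gender and gender-by-time as fixed effects, so that the model carries out the intention-to-treat statement. Use the same terms in the secondary mixed models for consistency. The by-time term is needed because a gender main effect alone would do almost nothing for a within-subject change contrast. Keep only gender's interaction with treatment in the exploratory moderator analyses.

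If the unadjusted model is preferred, the alternative is to remove the commitment to analyse by stratum and give the reason for omitting it.

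The cost is a sentence or two and a few degrees of freedom. Sample size, data collection and trial conduct are unchanged.

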### Recruitment and screening

All assessments will be conducted over the telephone, using protocols developed in our pilot studies and previous cohort work [42]. A research assistant (Researcher 1) will perform eligibility assessments and baseline data collection (see Table 2). A second research assistant (Researcher 2) will perform follow-up data collection. Participants, Researcher 2 and the study statistician will remain blind to participant allocation.

**Table 2 Tab2:** Trial measures

	Data collected	Method
Screening measures	Demographic information *Structured questions*	Standard demographic characteristics (e.g. age, gender, education level)
	Problem alcohol use *AUDIT*	Assessed by the Alcohol Use Disorders Identification Test (AUDIT) [33]. A score of > 6 for women and > 7 for men warrants inclusion in the study
	Severity of alcohol dependence *SADQ-C*	Assessed by the Severity of Alcohol Dependence Questionnaire (SADQ-C) [54]. A score of 31 or higher indicates “severe alcohol dependence” and warrants exclusion from the study
	Presence/severity of suicidal thoughts *SIDAS*	Assessed by the Suicidal Ideation Attributes Scale (SIDAS) [55]. A score of 21+ indicates high risk of suicidal behaviour and warrants exclusion from the study
	Other inclusion/exclusion *Structured questions*	Structured questions querying self-reported information pertaining to the study’s inclusion/exclusion criteria (e.g. history of psychosis)
Outcome measures		
Primary outcome	Alcohol problem severity *AUDIT*	The primary outcome is alcohol problem severity at 3 months, assessed by the AUDIT. The time frame has been adapted to cover month prior to assessment (rather than year), so that planned follow-up assessments at 3, 6 and 12 months can be performed. Five short items from the recent Australian Institute of Health and Welfare (AIHW) National Drug Strategy Household Survey have been included to provide additional information on self-reported change in alcohol use and alcohol literacy
Secondary outcomes	Alcohol use patterns *TLFB*	Past-month (30 days) alcohol consumption and heavy drinking days, assessed by the Alcohol Timeline Follow-back (TLFB) [35]. Heavy drinking days are measured as > 40/60 g of alcohol (4/6 standard drinks)
	Substance use *AOD Self-Completion Form*	Assessed using items from the Victorian Department of Health and Human Services (DHHS) Victorian AOD Self-Completion Form [56], recording recent use of other drugs and frequency of use in the past 28 days

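### The primary test subtracts baseline AUDIT instead of adjusting for it: valid and honestly powered, but about 26% to 34% of the information is lost at the plan's own variance components

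*Protocol article*

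**What the plan says.** Under Statistical analysis plan, the repeated outcomes are analysed by a linear mixed model with fixed effects for treatment, time and their interaction. For the primary outcome, "the primary comparison, between groups, of their changes from baseline to 3 months follow-up will be based on" a t test of the matching interaction contrast. The section sets no equality constraint on the arms' baseline means. Baseline alcohol use appears as a covariate only in the exploratory models that look for moderators.

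Under Sample size estimation, the same contrast is powered, using pilot estimates: "the between-subject variance component in the AUDIT score was 23.8, the within-subject variance component was 49.8 (intraclass correlation [ICC] = 0.323". The planning effect is a "reduction of at least 8 on the AUDIT score) in the R2C arm and that the control arm could exhibit a modest improvement of 4". Power is stated as 85% "with 120 evaluable subjects in each arm and assuming independence between subjects and equicorrelation within subjects". The target of 172 per arm allows for about 30% drop-out.

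Table 1 marks AUDIT at screening and at 3, 6 and 12 months, and not in the baseline column. The value used as baseline therefore appears to be the screening score.

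**The concern.** A change score removes baseline by subtracting all of it, whatever its correlation with the outcome. When that correlation is low, subtraction adds more noise than it removes. With equal variances, a change score is less precise than ignoring baseline altogether whenever the correlation is below 0.5, and the plan's own figure is 0.323.

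An analysis that adjusts for baseline weights it by its actual correlation with the outcome and, in large samples, is never less precise than the change score. What is at stake is the width of the primary confidence interval and the chance of missing a real 4-point benefit. Bias and type I error are not at issue.

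**Working it through.** **Inputs (Sample size estimation).** Between-subject variance 23.8; within-subject variance 49.8; equicorrelation; difference between arms 8 − 4 = 4 points; 120 evaluable per arm; two-sided 5% level; 120 inflated to 172 per arm, so 52 expected drop-outs per arm.

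**1. Total variance and correlation.** 23.8 + 49.8 = 73.6. r = 23.8/73.6 = 0.323, as stated.

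**2. The plan's own power.** The variance of a change score is 2 × 49.8 = 99.6. SE = √(2 × 99.6/120) = 1.288. Power by the non-central t distribution is 87%, against the stated 85%. The overall F test gives 90.5%, against the stated 90%. The stated figures are met or slightly conservative.

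**3. Three uses of baseline, 120 complete per arm.** With complete data and a free mean for each arm at each time, the interaction contrast equals the difference in mean change under any covariance model. Choosing the covariance by Akaike's criterion therefore cannot recover the loss.

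| Analysis | Variance per subject | SE | Power at 4 points |
|---|---|---|---|
| Change (planned) | 2 × 49.8 = 99.6 | 1.288 | 87% |
| 3-month score alone | 73.6 | 1.108 | 95% |
| Baseline-adjusted | 73.6 × (1 − 0.323²) = 65.9 | 1.048 | 97% |

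Adjusted/change = 65.9/99.6 = 0.66, which equals (1 + r)/2. The loss is 34% against adjustment, and 1 − 73.6/99.6 = 26% against ignoring baseline. A generalised least squares calculation on the four-time-point model gives the same standard errors: 1.288 with free baseline means and 1.048 with a common baseline mean.

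**4. With the expected drop-out.** Assume that the 52 drop-outs per arm contribute a baseline score only and stay in the mixed model.
- Planned contrast: variance = 2 × 73.6 × [(1 − r²)/120 + (1 − r)²/172] = 1.490; SE 1.221; power about 90%.
- Common baseline mean or covariate adjustment: variance = 2 × 65.9/120 = 1.098; SE 1.048; power 97%.
- Ratio 1.098/1.490 = 0.74, a loss of about 26%. The planned SE is still above the 1.108 obtained by ignoring baseline.

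**5. Sensitivity to the correlation** (complete data, equal variances). Loss = 1 − (1 + r)/2 = (1 − r)/2: 40% at r = 0.2, 34% at 0.323, 25% at 0.5 and 15% at 0.7.

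**6. Sensitivity to unequal spread** (complete data). Let k be the screening SD divided by the 3-month SD. The documents do not give k, so the values below are assumptions, with r held at 0.323. Adjusted/change = (1 − r²)/(1 + k² − 2rk).
- k = 0.6: ratio 0.92, loss 8%
- k = 0.75: ratio 0.83, loss 17%
- k = 1: ratio 0.66, loss 34%
- k = 1.25: ratio 0.51, loss 49%

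Change is less precise than ignoring baseline only when k > 2r, about 0.65.

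**The case against.** The strongest reply is that nothing here is an error. The planned contrast is unbiased, it is the contrast that was powered, and it meets its stated power. That stands: this is a recommendation for a better estimator.

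The size is also uncertain. The variance components come from a single-arm pilot of 34 people who received an earlier version of the intervention. Eligibility requires an AUDIT above 6 (women) or 7 (men). If that truncation narrows the screening SD relative to the 3-month SD, the loss shrinks, and for k below about 0.65 the change score would even beat ignoring baseline. Both points stand. They affect the size, but adjustment remains at least as precise in every case in steps 5 and 6.

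The protocol also defers the covariate list and analysis details to a statistical analysis plan that is not shown. This reply is weaker, because the primary contrast is already named and powered in the protocol itself.

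A reader might infer three stronger points that the documents do not support.
- **A mismatch with the primary outcome.** The abstract says "The primary outcome is the Alcohol Use Disorders Identification Test (AUDIT) score administered at 3 months post-baseline", while the test uses change. Under randomisation both contrasts estimate the same effect, and Sample size estimation expressly calls the 3-month interaction contrast the analysis of the primary outcome.
- **A different recall window at screening.** Table 2 says of the outcome AUDIT "The time frame has been adapted to cover month prior to assessment (rather than year", and gives the follow-up schedule as the reason. It does not say which window the screening AUDIT used, so a difference would be a guess.
- **A smaller trial.** By normal approximation, 85% power needs 112 evaluable per arm with change and 74 with adjustment. With 285 of 344 already randomised, the gain would come as precision and not as fewer participants.

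**Conclusion.** The point holds as a matter of efficiency. The primary test is valid and its 85% power is not overstated, but it discards information that the trial already collects. On the plan's variance components, with equal variances and equicorrelation, the loss against a baseline-adjusted analysis is 34% with complete data and about 26% if the expected drop-outs supply baseline only. A loss of about a third is therefore the complete-data figure, and about a quarter is nearer to the plan's own drop-out assumption. On those two bases, the chance of missing a true 4-point difference falls from about 13% or 10% to about 3%.

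The direction is secure. The size is not, because it depends on the pilot correlation and on the ratio of the screening SD to the 3-month SD, which the protocol does not report.

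**What to change.** Before database lock, specify the primary estimate as the between-arm difference in AUDIT at 3 months, adjusted for screening AUDIT. The 3-, 6- and 12-month scores are the responses, with treatment, time and treatment × time as fixed effects and screening AUDIT and screening AUDIT × time as covariates. The alternative is to keep the pre-randomisation score as a response and constrain the two arms to a common baseline mean, which randomisation justifies. Choose one form in advance, and keep the planned change contrast as a sensitivity analysis.

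The cost is a sentence or two in the analysis plan. No new data are needed, and the sample size stays as it is. The Cost effectiveness section already adjusts for baseline values of the outcome, so the approach is not foreign to the plan. On the plan's assumptions the stated 85% power becomes conservative.
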